## Abstract

**Background:**

Scalds are one of the most common forms of thermal injury in young children worldwide. Childhood scald injuries, which mostly occur in the home, result in substantial health service use and considerable morbidity and mortality. There is little research on effective interventions to prevent scald injuries in young children.

**Objectives:**

To determine the relationship between a range of modifiable risk factors for medically attended scalds in children under the age of 5 years.

**Design:**

A multicentre case-control study in UK hospitals and minor injury units with parallel home observation to validate parental reported exposures. Cases will be 0–4 years old with a medically attended scald injury which occurred in their home or garden, matched on gender and age with community controls. An additional control group will comprise unmatched hospital controls drawn from children aged 0–4 years attending the same hospitals and minor injury units for other types of injury. Conditional logistic regression will be used for the analysis of cases and matched controls, and unconditional logistic regression for the analysis of cases and unmatched controls to estimate ORs and 95% CI, adjusted and unadjusted for confounding variables.

**Main exposure measures:**

Use of safety equipment and safety practices for scald prevention and scald hazards.

**Discussion:**

This large case-control study will investigate modifiable risk factors for scalds injuries, adjust for potential confounders and validate measures of exposure. Its findings will enhance the evidence base for prevention of scalds injuries in young children.

## Introduction

Burn injuries in children under 10 years of age are a major cause of death internationally, and are the fifth most common cause of non-fatal childhood injuries.^1^ In those under 5 years, scalds are the leading cause of thermal injuries in high, middle and low income countries.^2–14^ Scalds accounted for 62% of hospital admissions for thermal injuries in children under 5 years old in the USA between 2003 and 2012,^15^ and 63% of such admissions in the same age group in England in 2012–2013.^16^ In 2012–2013 over 3500 children aged 0–14 years were admitted to hospital in England with a thermal injury, of which the majority (61%) were scalds.^16^ Most scalds in childhood occur at home^12^
^13^
^17^ and are most commonly caused by hot liquids from kettles, baths, cups or mugs.^17^^–^19

Paediatric scald injuries impose a heavy financial burden on the state. More severe scalds may require intensive care, skin grafts and months or years of rehabilitation.^2^ Studies from England suggest the average cost of treating an uncomplicated minor (<10% total body surface area) paediatric scald in 2002–2003 was £1850^20^ while the average cost of acute inpatient treatment of a ‘major scald’ (30–40% total body surface area) in 2007–2009 in a paediatric burns unit can be as high as £55 000.^21^ Socioeconomic disadvantage increases the risk of scalds. Recent research from the UK demonstrates that children living in the most disadvantaged areas have an 82% higher odds of a medically attended scald injury than those in the most affluent areas.^22^ This pattern is repeated globally, with socioeconomic differentials between and within countries.^12^
^13^
^23^

Systematic reviews and recent meta-analyses have consistently demonstrated that interventions to promote thermal safety in the home can increase safety behaviour and the use of safety equipment to reduce the risk of thermal injuries.^24–31^ However, there remains little evidence that they reduce the actual incidence of thermal injuries due to a lack of adequately powered randomised controlled trials or high quality observational studies. Rigorous case–control studies have often provided the best evidence for effective interventions in injury prevention.^32–34^ There are few case–control studies investigating prevention practices in the homes of scalded children.^23^
^35–37^ One Canadian multicentre study, exploring risk and protective factors for a range of childhood injuries requiring emergency department (ED) attendance in children under the age of 8 years, failed to find any significant associations between any scald prevention practices and ED attendance.^35^ A second study of children of all ages attending EDs in two hospitals in Greece with a thermal injury found a 40% reduction in the odds of injury with a one unit increase in a burn avoidance index which measured four scald prevention behaviours.^36^ Another study, of children aged 0–5 years attending an Iraqi hospital with an acute burn injury found a one unit increase in the number of thermal hazards increased the odds of a thermal injury by 32%.^23^ Finally a study of children aged 0–4 years attending EDs in 14 Dutch hospitals found that using a vacuum flask rather than cups or mugs, to store hot drinks halved the odds of ED attendance for a thermal injury.^37^ These studies were limited by small sample sizes,^36^
^37^ the use of hospital controls,^23^
^35^
^36^ the use of unvalidated parental reports to measure exposures,^23^
^36^
^37^ case definitions covering a wide range of injury mechanisms^35^ and potential bias from unmeasured confounders.^23^
^35–37^

The aim of the case–control study described in this protocol is to examine the relationship between modifiable risk factors and scald injuries in young children. Community and hospital controls will be used and a range of confounding factors will be measured and adjusted for. Parental reported exposures will be validated by home observations in a sample of cases and controls.

## Methods

### Objectives

The objective of this case–control study is to determine the relationship between a range of modifiable risk factors and medically attended scalds in children under the age of 5 years.

### Study design

A multicentre case–control study will be carried out within hospitals and minor injury units (MIUs) in Nottingham, Bristol, Derby, Gateshead, Great Yarmouth, Newcastle upon Tyne, Norwich and Lincoln, UK. This is one of a series of case-control studies running concurrently in these study centres which employ identical methods and aim to identify modifiable risk factors for different injury mechanisms. The published protocol for the falls case–control study describes the methods in more detail.^38^

### Definition of cases and controls

Cases will be defined as children under the age of 5 years who received medical attention for a scald injury which occurred in their home or garden, defined as the address at which they were registered with a family doctor or general practitioner (GP). Scald injuries are defined as ‘thermal injuries caused by hot liquids or steam’. Medical attention is defined as an admission to hospital or attendance at an ED or MIU. Children are not eligible to take part if the injury was intentional or suspected to be intentional or if the child lives in residential care. Fatal injuries will not be included to avoid parental distress. Cases are not eligible to be included as a control in the study at any time after being recruited as a case.

Controls are defined as children under the age of 5 years who did not receive medical attention for a scald injury on the date of the case's medical attendance. Children living in residential care are not eligible to participate in the study. Controls are eligible for recruitment to the study as a case or as a further control if they are recruited at least 12 months after their first recruitment. Controls will not be recruited more than twice to the study.

### Recruitment of cases and controls

Participants will be recruited during or after their hospital admission or attendance at the ED or MIU. The initial approach to potential participants will be made by clinical staff, followed by contact from researchers where agreement for this is given. Researchers will contact potential participants during their medical attendance, or by telephone or postal invitation within 72 h of ED or MIU attendance. Postal and telephone reminders will be used if no response is received within 2 weeks. Participants will be given a £5 voucher for local stores to thank them for participation in the study.

Controls will be recruited from the community (matched community controls) and from the hospital (unmatched hospital controls). Community controls will be identified from the GP practice where the case is registered, and matched with the case on age (within 4 months) and gender. If the GP practice where the case is registered does not consent to take part, the GP practice closest to the case's GP practice will be asked to recruit controls. GPs or Primary Care Trust staff will invite, by post, parents or guardians (hereafter referred to as parents) of 10 children for each recruited case to take part in the study. One reminder will be sent to non-responders (controls and cases) if they have not replied within 2 weeks of initial mailout. Hospital controls will comprise children already recruited as a case to one of the other ongoing case–control studies, that is, these will be children aged 0–4 years attending the ED or MIU with another injury mechanism (fall on the same level, fall from furniture, staircase fall or poisoning).

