### Definition of exposures and confounding variables

Exposures relating to scalds will be categorised into safety (and other potentially risk reducing) equipment use, safety behaviours and home hazards (see table 1). Cases will be asked about exposures relating to the 24 h (or 1 week for less frequent behaviours) before the scald injury. Controls will be asked about exposures for the 24 h (or 1 week for less frequent behaviours) prior to completing the questionnaire. A range of potential confounding factors will be measured as shown in table 1.

**Table 1 INJURYPREV2014041255TB1:** Definition of exposures and confounding variables

*Exposure: Safety and other potentially risk reducing equipment use* Use of safety gates Kettles with curly or short cables Play pens (or travel cots) Stationary activity centres *Exposure: Safety behaviours* Not drinking hot drinks while holding a child Not passing hot drinks over a child Keeping hot drinks out of reach of children Storing kettles at back of work tops Use of back rings on cooker Turning saucepan handles away from edge of cooker Not using tablecloths Knowledge of hot tap water/thermostat temperature Using cold water first when running a bath Measuring bath water temperature Not leaving child without an adult in the bath or bathroom Not having children running baths Teaching children safety rules about hot liquids *Exposure: Home hazards* Has baby walker	*Potential confounders: sociodemographic* Age Gender Ethnic group Family size and structure Housing tenure Receipt of state-provided means-tested benefits Single parenthood Adult unemployment in the household Overcrowding Deprivation (measured using the Index of Multiple Deprivation^39^) Distance of residence from hospital Use of out-of-home childcare *Potential Confounders**:** child and parent measures for health and behaviour* Child behaviour (infant, early child and child behaviour questionnaires)^40–42^ Child health status (VAS^43^; PedsQL^44^ ^45^) Long-term health conditions Parental mental health (Hospital Anxiety and Depression Scale)^46^ Parenting daily hassles^47^ ^48^ Parental perception of child's ability to reach hot liquids (a series of questions on climbing, reaching, turning on taps, ability to open safety gates)

PedsQL, pediatric quality of life inventory; VAS, visual analogue scale.

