### Analysis

The analysis of the validation of exposures has been described in the falls case–control study protocol.^38^ Relationships between exposures, potential confounding variables and scalds will be explored using causal diagrams. These will be used to identify the minimal set of potential confounding factors to adjust for when estimating ORs. Exposure and confounding variables will be described using frequencies and percentages for categorical variables and means (and SDs) or medians (and IQRs) for continuous variables as appropriate.

Conditional logistic regression will be used for the analysis of cases and matched controls to estimate ORs and 95% CIs, unadjusted and adjusted for confounding variables. All models will a priori adjust for deprivation and distance from hospital. Unconditional logistic regression will be used for the analysis of cases and hospital controls. All models will a priori be adjusted for age, gender, deprivation and distance from hospital, in addition to other potential confounding variables, as described for the matched analysis. Effect modification will be investigated by adding interaction terms to models and where present (p<0.01), stratified results will be reported. Results will also be stratified by the type of service used (child treated in ED or admitted to hospital vs no treatment required) as a proxy for injury severity.

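### For four of the 18 listed exposures, the hospital-control ORs can be biased, because those controls are selected on injuries that the exposure may itself influence

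*Protocol article*

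**What the plan says.** Under Recruitment of cases and controls, the Protocol article fixes the second control group: "Hospital controls will comprise children already recruited as a case to one of the other ongoing case–control studies". These are children "attending the ED or MIU with another injury mechanism (fall on the same level, fall from furniture, staircase fall or poisoning". Under Study design, the sister studies that supply them "employ identical methods and aim to identify modifiable risk factors for different injury mechanisms".

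Table 1 lists 18 exposures: four items of equipment, 13 behaviours and one home hazard. The equipment items are "Use of safety gates Kettles with curly or short cables Play pens (or travel cots) Stationary activity centres" and the hazard is "Has baby walker".

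The Analysis section then states: "Unconditional logistic regression will be used for the analysis of cases and hospital controls". It continues: "All models will a priori be adjusted for age, gender, deprivation and distance from hospital", with further confounders chosen from causal diagrams. All four control mechanisms serve as one group, whatever the exposure.

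The Abstract calls the hospital controls additional, and the Sample size section is written for cases and matched community controls only.

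**The concern.** A control group should show how common the exposure is in the population that produced the cases. Children recruited because of a fall or poisoning do so only for exposures unrelated to those injuries. Safety gates and staircase falls are the plainest counter-example. Play pens, activity centres and baby walkers plausibly bear on falls too, and gates may also limit access to poisons. If a gate prevents staircase falls, children without gates are over-represented among staircase-fall controls, and the scald OR for gates is measured against the wrong baseline.

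This is selection on an effect of the exposure, not confounding. The distortion is present within every stratum of age, gender, deprivation, distance and any other covariate, so no adjustment set removes it.

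The four exposures are three of the four equipment items and the only listed hazard. The Discussion expects the findings to inform home safety equipment schemes, so a distorted OR for these items could be read as failing to confirm a real community-control result, or as a finding in its own right.

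**Working it through.** **The plan's own figures.** The plan gives no figure for the hospital-control comparison. The Sample size section gives a target OR of 0.64, equivalent to 1/0.64 = 1.56 for a risk factor, and 259 × 4 = 1036 matched controls. These agree with one another. Only the OR of 0.64 is used below, as the true scald effect.

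**Assumptions not in the documents.**
- p: exposure prevalence in the source population, 0.5 (varied below).
- s: share of hospital controls whose injury the exposure affects.
- ORc: OR of the exposure for that control injury.
- All injuries are rare, and the remaining controls have prevalence p.

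**Formulas.**
1. Prevalence in affected controls: pf = p·ORc / (1 + p(ORc − 1)).
2. Prevalence in the pooled hospital controls: pc = s·pf + (1 − s)·p.
3. Expected OR = 0.64 × [p/(1 − p)] / [pc/(1 − pc)].

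With s = 1 this reduces to 0.64/ORc at any prevalence.

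**Mild case (ORc 0.80, s = 0.25).** pf = 0.40/0.90 = 0.444. pc = 0.111 + 0.375 = 0.486, odds 0.946. Expected OR = 0.64/0.946 = 0.68.

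**Strong case (ORc 0.50, s = 0.50).** pf = 0.25/0.75 = 0.333. pc = 0.167 + 0.250 = 0.417, odds 0.714. Expected OR = 0.64/0.714 = 0.90.

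**Range, true scald OR 0.64, p = 0.5:**

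| ORc | s = 0.25 | s = 0.50 | s = 1 |
|---|---|---|---|
| 0.50 | 0.76 | 0.90 | 1.28 |
| 0.64 | 0.71 | 0.80 | 1.00 |
| 0.80 | 0.68 | 0.72 | 0.80 |
| 1.00 | 0.64 | 0.64 | 0.64 |
| 1.25 | 0.61 | 0.57 | 0.51 |

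The first three rows are effects in the same direction on scalds and on the control injury: the OR moves towards the null, and past it in one cell. The last row is an opposite effect: the OR moves away from the null.

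**Exposure with no effect on scalds (true OR 1.0), ORc 0.50.** At s = 0.20, 0.33 and 0.50 the control odds are 0.875, 0.80 and 0.714. The expected ORs are 1/0.875 = 1.14, 1/0.80 = 1.25 and 1/0.714 = 1.40, so an inert exposure looks harmful.

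**Risk factor (true OR 1.56).** At s = 0.25, 0.50 and 1, ORc 1.56 gives 1.40, 1.25 and 1.00; ORc 2 gives 1.32, 1.12 and 0.78.

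**Sensitivity to prevalence.** In the strong case, p = 0.2 gives pc = 0.5 × 0.111 + 0.5 × 0.2 = 0.156, odds 0.184, and an OR of 0.16/0.184 = 0.87. With p = 0.8, pc = 0.5 × 0.667 + 0.5 × 0.8 = 0.733, odds 2.75, and the OR is 2.56/2.75 = 0.93. Prevalence matters less than s and ORc.

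**The case against.** The case against giving this much weight is substantial.

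- **Reach.** The argument covers four of 18 exposures. Hot drinks, kettles, saucepans and bath water have no evident causal path to falls or poisoning. A reader might infer that the whole hospital-control analysis is invalid; Table 1 does not support that. This stands.
- **Role.** The hospital controls are additional, the sample size was set for the matched analysis, and the objective can be answered without the affected comparison. This stands and limits the severity.
- **Direction and size.** A reader might infer that these ORs are certainly biased towards the null. The documents do not show that gates, play pens, activity centres or walkers affect falls or poisoning, or in which direction. The Study design section states only an aim to look for risk factors. The mix of control injuries is not given either. Direction and size therefore remain conditional, and the mild case (0.68 against 0.64) is small.
- **Design.** The Introduction names hospital controls as a limitation of earlier studies, and the Discussion lists the use of both control groups among the ways to limit bias. The two groups have different weaknesses, and comparing their ORs may expose a discrepancy. This stands in part: a discrepancy could be seen, but the hospital-control OR would remain biased.
- **Condensed article.** Exclusions by exposure might be in the full protocol or an analysis plan not shown. That would answer a complaint about missing detail. Here, however, the article itself fixes who the hospital controls are and compares cases with them. The causal diagrams it mentions serve to choose confounders, which does not address selection of controls.

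**Conclusion.** The concern holds in a limited form. For safety gates, play pens or travel cots, stationary activity centres and baby walkers, the hospital-control ORs can be biased by the way the controls are selected, and the planned adjustment cannot remove this. The sign depends on how each exposure acts on the control injuries relative to scalds. With effects in the same direction and 50% exposure, a true OR of 0.64 would be expected to appear as about 0.68 to 0.90 over the partial-share scenarios, and as 1.00 if every control injury shared the effect. These are scenarios resting on assumed prevalence, shares and control-injury effects, not estimates for this study. The matched community-control analysis and the scald-specific exposures are untouched by this mechanism. Severity is moderate, confined to the secondary comparison.

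**What to change.** Amend the Analysis section for these four exposures only:

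1. Extend the planned causal diagrams to include the four control injuries. Before the data are examined, list for each exposure the mechanisms it may influence.
2. Exclude children with those mechanisms from the hospital-control group for that exposure. The list should follow the diagram rather than habit: for gates it should include poisoning as well as staircase falls, if the diagram shows that path.
3. Report the pooled hospital-control group as a sensitivity analysis.
4. Where every mechanism may be affected, state that the OR compares scald with other injury rather than with the source population.
5. Base conclusions for these four exposures on the community-control OR.

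This changes analysis wording only; no new data are needed and the matched analysis stays as it is. The cost is fewer hospital controls and less precision for these exposures, and control sets that differ between exposures, so their hospital-control ORs are less directly comparable with the rest.

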### Definition of exposures and confounding variables

Exposures relating to scalds will be categorised into safety (and other potentially risk reducing) equipment use, safety behaviours and home hazards (see table 1). Cases will be asked about exposures relating to the 24 h (or 1 week for less frequent behaviours) before the scald injury. Controls will be asked about exposures for the 24 h (or 1 week for less frequent behaviours) prior to completing the questionnaire. A range of potential confounding factors will be measured as shown in table 1.

**Table 1 INJURYPREV2014041255TB1:** Definition of exposures and confounding variables

*Exposure: Safety and other potentially risk reducing equipment use* Use of safety gates Kettles with curly or short cables Play pens (or travel cots) Stationary activity centres *Exposure: Safety behaviours* Not drinking hot drinks while holding a child Not passing hot drinks over a child Keeping hot drinks out of reach of children Storing kettles at back of work tops Use of back rings on cooker Turning saucepan handles away from edge of cooker Not using tablecloths Knowledge of hot tap water/thermostat temperature Using cold water first when running a bath Measuring bath water temperature Not leaving child without an adult in the bath or bathroom Not having children running baths Teaching children safety rules about hot liquids *Exposure: Home hazards* Has baby walker	*Potential confounders: sociodemographic* Age Gender Ethnic group Family size and structure Housing tenure Receipt of state-provided means-tested benefits Single parenthood Adult unemployment in the household Overcrowding Deprivation (measured using the Index of Multiple Deprivation^39^) Distance of residence from hospital Use of out-of-home childcare *Potential Confounders**:** child and parent measures for health and behaviour* Child behaviour (infant, early child and child behaviour questionnaires)^40–42^ Child health status (VAS^43^; PedsQL^44^ ^45^) Long-term health conditions Parental mental health (Hospital Anxiety and Depression Scale)^46^ Parenting daily hassles^47^ ^48^ Parental perception of child's ability to reach hot liquids (a series of questions on climbing, reaching, turning on taps, ability to open safety gates)

PedsQL, pediatric quality of life inventory; VAS, visual analogue scale.

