### Measurement of exposures and confounding variables

Exposures and confounding factors will be measured using parent-completed questionnaires, specific to the age of the child (0–12 months, 13–36 months and 37–59 months). The development, piloting and validation of the questionnaires are described in the protocol for the falls case–control study.^38^

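### Parental mental health, daily hassles and child health are reported after the scald with no stated pre-injury reference period; if chosen as adjusters, show the matched ORs with and without them

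*Protocol article*

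**What the plan says.** All references are to the protocol article.

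- **Timing (Recruitment of cases and controls).** "Participants will be recruited during or after their hospital admission or attendance at the ED or MIU". Community controls are invited by post through GP practices, and no injury is required of them. Hospital controls are children already recruited as cases, for another type of injury, in the parallel studies.
- **Instrument (Measurement of exposures and confounding variables).** "Exposures and confounding factors will be measured using parent-completed questionnaires, specific to the age of the child".
- **Reference period (Definition of exposures and confounding variables).** For exposures, "Cases will be asked about exposures relating to the 24 h (or 1 week for less frequent behaviours) before the scald injury". For confounders the text says only "A range of potential confounding factors will be measured as shown in table 1".
- **Candidates (Table 1).** The list includes "Parental mental health (Hospital Anxiety and Depression Scale"), "Parenting daily hassles", "Child health status (VAS" and PedsQL), and "Parental perception of child's ability to reach hot liquids".
- **Selection (Analysis).** Causal diagrams will pick the smallest sufficient adjustment set. The only variables fixed in advance are deprivation and distance from hospital, plus age and gender in the hospital-control analysis. ORs are reported unadjusted and adjusted.

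**The concern.** The authors saw that timing matters and tied case exposures to a short window before the injury. The Discussion repeats that safeguard for exposures, but for confounders it cites only the use of validated tools. Three of the listed measures can change quickly. A parent whose child has just been scalded may score differently on anxiety, depression and hassles, and may rate the child's health differently. Parents of community controls have had no such event.

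A causal diagram drawn from Table 1 would plausibly show parental mental health as a common cause of safety practice and scald, and so could select it. The fitted model would then use the score recorded after the injury in place of the state before it. The study is sized for an OR of 0.64, so a moderate distortion could hide or exaggerate the effects it is meant to detect.

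**Working it through.** **Inputs.** The OR of 0.64 comes from the Sample size section. Nothing else needed is in the article, so the following are assumptions:

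- g: how many SD lower the pre-injury score is in families using the safe practice;
- c: log OR for scald per SD of the pre-injury score, given the practice;
- d: how many SD the injury raises the recorded score in cases.

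**Formulas.** Take a rare outcome and a roughly normal score with SD 1. Given the practice, the recorded score in cases then lies c + d above that in controls. This gives

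- OR without the score = 0.64 × exp(−g × c)
- OR with the recorded (shifted) score = 0.64 × exp(+g × d)
- OR with the true pre-injury score = 0.64

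**Effect of adjusting for the shifted score.** The simulation is an unmatched logistic model with four controls per case and c = 0.2.

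| g | d | Formula | Simulation |
|---|---|---|---|
| 0 | 0 to 0.8 | 0.64 | 0.63–0.64 |
| 0.29 | 0.2 | 0.64 × exp(0.058) = 0.68 | 0.68 |
| 0.29 | 0.5 | 0.64 × exp(0.145) = 0.74 | 0.75 |
| 0.29 | 0.8 | 0.64 × exp(0.232) = 0.81 | 0.82 |
| 0.55 | 0.2 | 0.64 × exp(0.110) = 0.71 | 0.73 |
| 0.55 | 0.5 | 0.64 × exp(0.275) = 0.84 | 0.86 |
| 0.55 | 0.8 | 0.64 × exp(0.440) = 0.99 | 1.02 |

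Adjusting for the pre-injury score gave about 0.64 throughout. With g = 0 there is no bias.

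**Direction.** If families using the safe practice score higher (g = −0.4) and d = 0.4, the result is 0.64 × exp(−0.16) = 0.55, away from the null.

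**Effect of leaving the score out.** With g = c = d = 0.4:

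- without the score: 0.64 × exp(−0.16) = 0.55
- with the shifted score: 0.64 × exp(+0.16) = 0.75

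The two errors are equal and opposite, each 0.16 on the log scale against ln(0.64) = −0.446, or about 36% of the log OR. Leaving the score out is the worse choice when c exceeds d, and adjusting is the worse choice when d exceeds c.

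**When the two estimates bracket the truth.** They do so when c and d have the same sign, for example when distress both raises scald risk and is raised by the scald. With opposite signs they need not. For g = 0.4, c = −0.2, d = 0.4 they are 0.64 × exp(0.08) = 0.69 and 0.64 × exp(0.16) = 0.75, both above 0.64.

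**What the data can show.** The two log ORs differ by g × (c + d), and cases and controls differ in recorded score by c + d. Both depend on the sum, so the study data alone cannot say how much is true confounding and how much is a consequence of the injury.

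**The case against.** The strongest defence has four parts.

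1. **Adjustment is not fixed.** These measures are candidates, and the causal diagrams can exclude a variable that the outcome affects. This is right, and it limits the point to a conditional one. The diagrams protect, however, only if the recorded score is drawn separately from the pre-injury state, and Table 1 makes no such distinction. The planned unadjusted ORs help little, because they drop every other confounder as well.
2. **The article is condensed.** Study design and Measurement of exposures and confounding variables refer to the falls study protocol, which is not shown. The items may ask case parents about the time before the injury. This also stands: a shift is a risk, not an established fact. Even with such wording, answers would still be given after the event.
3. **Hospital controls are also measured after an injury.** The differential shift should be smaller there, so the concern centres on the matched analysis. The two control groups could then disagree for this reason alone.
4. **Dropping the scores has its own bias.** The working shows that it can be as large as the bias from adjusting.

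A reader might infer something stronger: that all four measures, including perceived ability to reach hot liquids, are consequences of the scald and should be kept out of the main models. The documents do not support this. Table 1 describes the reach item as questions on climbing, reaching, taps and safety gates. These abilities mostly predate the scald, and at most the parent's report of them shifts. They plausibly drive both safety practice and scald risk, and age matching within 4 months controls them only in part.

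**Conclusion.** The point holds in a limited form. For parental mental health, daily hassles and child health status, the article places measurement in cases after the outcome, states no pre-injury reference period, and keeps the measures eligible for adjustment. If they are selected, the matched OR may be adjusted for a score partly changed by the injury.

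The size is unknown. With assumed shifts of 0.2 to 0.8 SD and a score about 0.3 SD lower in families using the safe practice, 0.64 becomes about 0.68 to 0.82. It stays at 0.64 if score and practice are unrelated, and moves away from the null if the relation is reversed. These figures rest on a rare outcome, a roughly normal score and a uniform shift in cases. Removing the scores outright is not justified, since omission can bias by a similar amount in the opposite direction.

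**What to change.** - In the causal diagrams, draw the recorded score for each of the three measures as a post-injury node, distinct from the pre-injury state it stands for.
- State the reference period of these items for cases, if the questionnaire sets one.
- Wherever one of the three enters an adjustment set, report the matched OR with and without it, keeping all other adjusters the same. Interpret cautiously any exposure effect that depends on the choice. Describe the pair as a likely bracket only where the pre-injury effect and the post-injury shift plausibly have the same sign.
- Keep the child's ability to reach hot liquids as a candidate confounder.

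The cost is a few sentences in the analysis section and one extra set of models to report. No design change or new data are needed.
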